## 7.4 Randomization

Participants who meet the study's eligibility criteria will be randomly assigned in a 1:1 ratio either to the control or the experimental arm. The randomization will be stratified by study site. The randomization will be conducted by the HPTN SDMC.

## 7.5 Blinding

This is an unblinded study. Participants are not blinded due to the nature of the intervention.

## 7.6 Analysis Plan

### 7.6.1 Primary Analysis

#### 7.6.1.1 Analysis of Feasibility

Feasibility will be evaluated by the following:

- 1.) The proportion of enrolled participants in the experimental arm who attend the first 4 intervention sessions in the first 2 weeks after enrollment out of all individuals randomized to the experimental arm. An estimate of the proportion is given by

$$P = \frac{A}{N}$$

where N is the total number of participants enrolled in the experimental arm and A is the number of individuals who attend the first 4 intervention sessions in the first 2 weeks among those N participants. Since the sample size is not large (about 23 per arm), the exact binomial confidence interval will be calculated for the estimated proportion.

2.) The proportion of enrolled participants in the experimental arm who attend the 4 intervention sessions and the fifth, booster session out of all individuals randomized to the experimental arm, and compared to the proportion of individuals who attend their CHAVI 001 visits at weeks 1, 2, and 8. The two-sided Fisher exact test will be used to test 2 proportions.

3.) The proportion of enrolled participants in the experimental arm who attend the first 4 intervention sessions at any time point after enrollment out of all individuals randomized to the experimental arm. This analysis will include participants who attended all of the first four intervention sessions but not necessarily within the 2 week period after enrollment. An estimate of the proportion is given by

$$P = \frac{A}{N}$$

where N is the total number of participants enrolled in the experimental arm and A is the number of individuals who attend the first 4 intervention sessions at any time point among those N participants.

Feasibility endpoints will be measured using session attendance records. Data from the quantitative assessments and qualitative interviews will not contribute to the analysis of the feasibility endpoints.

#### 7.6.1.2 Analysis of Acceptability

Data from the quantitative assessment and qualitative interviews will contribute to the analysis of the acceptability endpoints. Standard descriptive statistics, such as means, medians, variance, and interquartile ranges for continuous variables and proportions for binary variables will be used to summarize the format, content, and perceived effectiveness. For categorical variables, the numbers and the proportions will be tabulated. Analysis of the qualitative data related to acceptability is described below in Section 7.6.3 Qualitative Analysis.

#### 7.6.2 Secondary Analysis

Standard descriptive statistics, such as means, medians, variance, and interquartile ranges for continuous variables and proportions for binary variables will be used to summarize the characteristics of sexual behavior, depression, substance use, and motivation for safe sex at baseline and/or subsequent study visits in both study arms. For categorical variables, the numbers and the proportions will be tabulated. **Particularly, for each participant, the pre-post difference at each visit and the difference between current and previous visits will be visually explored to look for any trend using a single-case analysis approach. A case study and mixed-methods (e.g. using both qualitative and quantitative data) approach will also be considered in the single-case situation to better understand the intervention effect among particular study subjects. Some nonparametric smoothing will be considered to fit the longitudinal curves to further explore the trends.**

To assess the efficacy of the intervention on sexual behaviors, such as self-reported unprotected sex acts with the intervention, Poisson regression will be used for count endpoints based on generalized estimation equations (Liang, Zeger, et al., 1986). Effects of the intervention on sexual behaviors at each time point will be assessed to see whether there are differences in behaviors after the intervention or at any time. In addition, to determine whether there are changes in behavior after viral loads have stabilized, behaviors will be compared before and after 12 weeks post-diagnosis. A robust variance estimator will be used to correct for correlation among the longitudinal measures at baseline and post-intervention follow-up visits. If over-dispersion exists, quasi-Poisson or negative binomial model will be used. A Wald test will be used to test whether the intervention has significant effect on reducing sexual risk behaviors compared to the control arm. It will be a two-sided test at a significance level of 0.05. **Given all the participants are acute or early HIV-infected, it is possible that there may be few, if any, unprotected sex acts reported. Therefore, the negative binomial assumption might not hold and a non-parametric approach will be considered. Specifically, unprotected sex acts will be categorized into 2 or 3 groups. At each visit, a Fisher exact test will be used to test proportions difference for two arms and exact p-values will be calculated.**

The impact of mediator variables (Table 4) on mediating the effects of the intervention on self-reported unprotected sex behaviors will be assessed. Multivariate analysis of variance (MANOVA) will be used to determine the relationship between intervention and changes in the mediator variables with repeated measures over the visits if the normality assumption holds. For the categorical variables, Chi-squared tests will be used to test independence between intervention and mediator variables at each visit.

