### **5.1 Screening/Enrollment (Day 0)**

Screening and enrollment will most likely take place on the same day but may take place on different days based on the preferences of the study participants and availability of study staff. Individuals will be informed of their HIV test results and receive standard HIV post-test counseling for risk reduction as part of CHAVI 001. Thereafter participants will be introduced to HPTN 062. Only individuals with AHI who are enrolled in CHAVI 001 are eligible for screening for HPTN 062. Written informed consent will be obtained for HPTN 062 before study procedures are initiated. Participants who provide consent will be enrolled in the study and administered a baseline behavioral assessment. Participants will then be randomized to the experimental arm or control arm. Individuals randomized to the experimental arm will participate in the introductory intervention session (session 1), ideally on this day; however, due to time constraints the introductory intervention session may be scheduled later.

At the screening/enrollment visit, participants will receive the following:

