### 7.3 Sample Size and Accrual

A total of approximately 46 individuals diagnosed with acute and early HIV infection will be enrolled at two or more sites over a period of approximately 24 months. Individuals will be enrolled in HPTN 062 as soon as possible after being diagnosed with AHI through CHAVI 001. Each arm will have a total of approximately 23 participants. The sample size is limited by the expected low incidence rate for AHI (based on data available from the ongoing studies). For example, in the CHAVI 001 study, about 1 percent of subjects screened have been identified as acutely infected with HIV. Therefore, in the same or similar study settings, approximately 4600 individuals will need to be screened through other studies or programs to identify 46 individuals with AHI who may be eligible for and willing to participate in HPTN 062. Due to the limited sample size expected for this study (n=46), all sample-size calculations assume data will be pooled across sites.

Note: A minimum of 46 participants is targeted; however, the final number may be higher or lower, depending on the rate of accrual in CHAVI 001 during the HPTN 062 enrollment period of approximately 24 months.

Since the sample size is not large (about 23 per arm), the exact binomial confidence interval is calculated. Table 5 shows the expected precision (i.e. 95 percent CI) for estimates of proportions that will be obtained from this study as a function of the total sample size and the observed proportion. For example, for the proportion of participants who complete 4 intervention sessions in the first 2 weeks after enrollment, if the sample size is 23 in the experimental arm and the observed proportion is 0.8, the 95 percent CI for the proportion will be (0.58, 0.94). Proportions of adherence will be estimated separately for each arm.

**Table 5 - 95% CI for sample proportion as a function of observed proportion and sample size, e.g. 95% CI =(0.58, 0.94), if  $p = .8$  and  $n = 23$**

| Sample Size per arm, Pooling All Sites |              |              |              |              |              |
|----------------------------------------|--------------|--------------|--------------|--------------|--------------|
| Observed Proportion                    | 20           | 23           | 30           | 40           | 46           |
| 0.5                                    | (0.27, 0.73) | (0.29, 0.71) | (0.31, 0.69) | (0.34, 0.66) | (0.35, 0.65) |

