**Figure 2. Histogram of sex acts from simulated data under negative binomial distributions each with different mean ( $\mu$ ) and over-dispersion parameter ( $\phi$ ).**

[figure not shown]

**Table 6 - Power to detect a significant difference in self-reported unprotected sex acts between control and intervention groups. The type I error was set at 0.05 for a two-sided test.**

| Sample Sizes per Arm Pooling All Sites |                              |                         |       |      |      |       |      |      |       |      |      |
|----------------------------------------|------------------------------|-------------------------|-------|------|------|-------|------|------|-------|------|------|
| Control group mean (x1)                | Intervention group mean (x2) | Mean difference (x1-x2) | phi=1 |      |      | phi=2 |      |      | phi=5 |      |      |
|                                        |                              |                         | 20    | 23   | 30   | 20    | 23   | 30   | 20    | 23   | 30   |
| 1.5                                    | 0.5                          | 1.00                    | 0.90  | 0.93 | 0.98 | 0.63  | 0.68 | 0.79 | 0.39  | 0.42 | 0.50 |
| 2.0                                    | 0.5                          | 1.50                    | 0.99  | 1.00 | 1.00 | 0.87  | 0.90 | 0.96 | 0.56  | 0.61 | 0.70 |
| 2.5                                    | 0.5                          | 2.00                    | 1.00  | 1.00 | 1.00 | 0.96  | 0.97 | 1.00 | 0.70  | 0.75 | 0.84 |
| 2                                      | 1                            | 1.00                    | 0.74  | 0.80 | 0.89 | 0.45  | 0.50 | 0.61 | 0.27  | 0.29 | 0.34 |
| 2.5                                    | 1                            | 1.50                    | 0.95  | 0.98 | 0.99 | 0.72  | 0.77 | 0.87 | 0.44  | 0.46 | 0.55 |
| 3                                      | 1                            | 2.00                    | 1.00  | 1.00 | 1.00 | 0.88  | 0.92 | 0.97 | 0.57  | 0.62 | 0.71 |
| 2.5                                    | 1.5                          | 1.00                    | 0.60  | 0.67 | 0.79 | 0.35  | 0.39 | 0.49 | 0.21  | 0.22 | 0.27 |
| 3.0                                    | 1.5                          | 1.50                    | 0.89  | 0.93 | 0.98 | 0.60  | 0.65 | 0.77 | 0.34  | 0.37 | 0.44 |

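### Section 7.6.2 counts baseline among the GEE outcomes without naming the contrast tested, and its effectiveness analyses as described use neither the pre-randomization count nor the stratifying site

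*Protocol*

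**What the plan says.** Section 7.6.2 analyses count endpoints by Poisson regression with generalized estimating equations, moving to a quasi-Poisson or negative binomial model if there is over-dispersion. On the repeated measures it says: "A robust variance estimator will be used to correct for correlation among the longitudinal measures at baseline and post-intervention follow-up visits". A Wald test then compares the arms: "It will be a two-sided test at a significance level of 0.05". The section also plans to look at the intervention effect at individual time points and to compare behaviour before and after 12 weeks. If few unprotected acts are reported, the counts are grouped into two or three categories and the arms are compared by Fisher's exact test at each visit. No covariate is named in either analysis.

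Two other sections bear on this. Section 5.1 describes the baseline behavioural assessment and continues: "Participants will then be randomized to the experimental arm or control arm". Section 7.4 says: "The randomization will be stratified by study site".

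Section 7.3 states that the study is not powered for efficacy. Section 2.3 nevertheless gives assessment of an effect size, for use in planning a larger study, as one advantage of including a randomized comparison.

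**The concern.** The baseline count is collected before assignment, so the arms cannot differ there except by chance. It can be used as a covariate, or its mean can be held equal between arms. Treating it as one more outcome without naming the tested contrast leaves at least three analyses open:

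- one arm term across all visits;
- an arm contrast at follow-up visits only;
- a contrast of change from baseline.

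These differ in precision, and the first also differs in what it estimates.

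With about 23 participants per arm and skewed counts, a chance imbalance in prior behaviour is a real possibility. An unadjusted follow-up comparison carries that imbalance into the estimate. At stake is the quality of the rate ratio that would inform a later trial, and the power of the secondary test. The primary feasibility and acceptability results are not affected.

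**Working it through.** **Inputs from the protocol.** Size: "Each arm will have a total of approximately 23 participants" (7.3). Allocation: "randomly assigned in a 1:1 ratio either to the control or the experimental arm" (7.4). Test level in the power table: "The type I error was set at 0.05 for a two-sided test" (7.3), matching 7.6.2. Counts are negative binomial with variance φ × mean, φ = 1, 2 or 5. The headline case is a mean of 3 in control and 1 in intervention. Power is based on a single observation per participant, and "all sample-size calculations assume data will be pooled across sites" (7.3). There are eight follow-up assessments in section 2.3, and seven for unprotected acts in Table 4, which omits week 1.

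**Assumed, because the protocol gives no figure.** Within-person latent correlation 0.3, 0.5 or 0.7; baseline mean equal to the control follow-up mean; constant effect at all follow-up visits; no dropout; two equal sites.

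**Step 1: reproduce the plan's power.** Section 7.3 gives 92% (φ = 2) and 62% (φ = 5) for 3 vs 1 with 23 per arm. Normal approximation: SD = √[φ(3+1)/2], SE = SD × √(2/23).
- φ = 2: SD = 2, SE = 0.590, 2/0.590 − 1.96 = 1.43, power 0.924.
- φ = 5: SD = 3.162, SE = 0.932, 2/0.932 − 1.96 = 0.185, power 0.573.

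Simulating 10,000 trials with a quasi-Poisson Wald test gives 0.927 and 0.616. The stated figures reproduce.

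**Step 2: power under the specifications that the text leaves open.** 1,000 simulated trials per setting; baseline plus eight visits; correlated negative binomial counts; robust Wald test; φ = 5. Entries are for correlation 0.3/0.5/0.7.

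| Analysis | 2 vs 1 | 3 vs 1 |
|---|---|---|
| One arm term over baseline and follow-up | 0.57/0.42/0.33 | 0.94/0.81/0.70 |
| Follow-up visits only, unadjusted | 0.65/0.52/0.39 | 0.97/0.88/0.81 |
| Follow-up visits with log(baseline+1) | 0.74/0.68/0.70 | 0.99/0.97/0.98 |

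Gain of the third row over the second: 9/16/31 points at 2 vs 1, and 2/9/17 points at 3 vs 1. If the baseline mean is 6 rather than 3 in the 3 vs 1 case, power goes from 0.97/0.88/0.80 to 0.99/0.97/0.97, a similar gain.

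At 2.5 vs 1.5, φ = 5, a change-from-baseline contrast has power 0.31/0.39/0.51. This compares with 0.51/0.38/0.29 for follow-up only and 0.56/0.56/0.59 with the covariate.

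With no true effect, the robust Wald test rejected in about 6 to 9% of trials for all these models. Comparisons between models are therefore safer than the absolute levels. Monte Carlo error is up to √(0.25/1000) = 1.6 points.

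**Step 3: the rate ratio if one arm term spans all visits.** With baseline mean b in both arms and k follow-up visits, the pooled ratio is (b + k × 1)/(b + k × 3).
- b = 3, k = 7: 10/24 = 0.417.
- b = 3, k = 8: 11/27 = 0.407.
- b = 6, k = 8: 14/30 = 0.467.

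The true ratio is 1/3. On the log scale, ln 0.417/ln 0.333 = 0.80 and ln 0.407/ln 0.333 = 0.82, so with b = 3 the effect is 18 to 20% too small. With arm-by-visit or arm-by-period terms, or follow-up visits only, the estimate is about 0.32 to 0.33 and is not diluted.

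**Step 4: site.** Adding site to the baseline-adjusted model changes power by 0 to 3 points when the sites do not differ. At 2.5 vs 1.5, φ = 5, it goes from 0.52 to 0.55 with a 1.5-fold site difference. An extreme threefold difference gives 0.50 to 0.56.

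**Step 5: is the baseline count usable as a covariate?** The narrative of section 5.1 puts the assessment before randomization. The activity list beneath it names randomization first, but does not claim to be in time order.

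**The case against.** The strongest reply is that section 7.6.2 never writes out the model. It excludes no covariate, and covariates and mean-model terms are commonly left to an SAP, which is not at hand. That stands: silence is not a decision against adjustment, and a missing covariate list alone would not be a finding. What remains is what the protocol does state: baseline belongs to the response series, one Wald test has no named term, and the fallback is a plain per-visit Fisher test.

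A reader might infer that the planned estimate is pulled toward 1. The documents do not support this. The sentence that mentions baseline concerns the variance, and the planned look at effects by time point fits a model with no dilution. A per-visit Fisher test cannot be diluted by baseline either. The pull toward 1 is a consequence of one possible reading only.

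It can also be said that an arm-by-time contrast against baseline already corrects chance imbalance. It does, but at low correlation it costs power relative to using follow-up alone (0.31 against 0.51 in step 2), while the covariate does at least as well as either at all three correlations.

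Nor do the documents show that baseline is a strong predictor. They give no correlation, and section 1.2 reports that many participants changed their behaviour after diagnosis. The gain could therefore lie at the low end.

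Finally, a reader might base site adjustment on country differences in CHAVI 011. Section 1.2 gives only qualitative contrasts from 37 interviews and describes condom use as similar in both countries. The sites of this trial are not fixed either. The argument for site rests on the stratified randomization alone.

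**Conclusion.** The point holds as an incomplete and inefficient specification. It does not show an invalid test or a biased estimate. As described, the effectiveness analyses leave the tested contrast open and make no use of a baseline count taken before randomization or of the stratification factor.

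Under the planned type of model at 2 vs 1 and φ = 5, adjusting for baseline would add about 9 to 31 power points for correlations from 0.3 to 0.7. At 3 vs 1 the gain is about 2 to 17 points. These sizes rest on assumed correlations, a constant effect, no dropout and φ = 5, the protocol's severe level of over-dispersion. Dilution to about 0.41 to 0.42 is conditional on a single pooled arm term. Site adds little beyond baseline unless sites differ greatly.

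Severity is minor to moderate. The endpoint is secondary and the protocol says that it is not powered for efficacy, but the effect-size estimate is a stated purpose of the control arm.

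**What to change.** In section 7.6.2 or the SAP:

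- State that the intervention effect is the arm contrast over post-baseline visits, and that the Wald test addresses this contrast. Visit-specific effects can be reported beside it.
- Include log(baseline acts + 1) as a covariate, or keep baseline in the response with its mean constrained equal between arms.
- Add site as a stratification term if more than one site enrolls; with one site it drops out.
- Replace the plain per-visit Fisher test with a site-stratified or baseline-adjusted exact test as the sparse-data fallback.
- Confirm in section 5.1 that the baseline assessment is completed before assignment.

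The cost is wording. Both variables are already collected, and neither the sample size nor any visit changes.

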| 0.6                                    | (0.36, 0.81) | (0.38, 0.80) | (0.41, 0.77) | (0.43, 0.75) | (0.45, 0.74) |
| 0.7                                    | (0.46, 0.88) | (0.48, 0.87) | (0.51, 0.85) | (0.53, 0.83) | (0.55, 0.83) |
| 0.8                                    | (0.56, 0.94) | (0.58, 0.94) | (0.61, 0.92) | (0.64, 0.91) | (0.66, 0.90) |
| 0.9                                    | (0.68, 0.99) | (0.70, 0.98) | (0.73, 0.98) | (0.76, 0.97) | (0.78, 0.97) |

Note that this study is not powered to evaluate the efficacy of the intervention effect. The sample size is limited by the availability of subjects diagnosed with the AHI. Table 6 displays the power of detecting efficacy for a range of hypothesized true values of the effect size at the 0.05 significance level. The powers in the table were estimated by a simulation of 10,000 trials under the assumption that the numbers of self-reported unprotected sex acts in the control and intervention arms are distributed as a negative binomial random variable with mean  $\mu$  and variance  $\phi \cdot \mu$  ( $\phi$  is the over-dispersion parameter). The negative binomial distribution is a mixture of Poisson distributions with mean distributed as a Gamma distribution with scale parameter,  $(1 - p)/p$ , and shape parameter,  $r$ . So the mean  $\mu$  is equal to  $r \cdot (1 - p)/p$  and variance  $r \cdot (1 - p)/p^2$  with  $\phi = 1/p$ . For  $\phi = 1$ , the mean and the variance are the same, such that the number of self-reported sex acts are simply Poisson distributed with no over-dispersion. Figure 2 gives the histogram of simulated sex acts under different negative binomial distributions. Simulations were done for three levels of over-dispersion: none ( $\phi = 1$ ), mild ( $\phi = 2$ ), and severe ( $\phi = 5$ ). The powers were estimated based on a cross-sectional study, i.e., a single observation per subject. Higher power will likely be obtained for this study because of longitudinal data being collected. Although the study is not sufficiently powered, if the effectiveness of the intervention is truly high, a sample size of 23 in each group would yield 92 percent (62 percent) power to detect the mean difference of 2 in self-reported unprotected sex acts in two groups assuming over-dispersion parameter of 2 (5) if the mean of sex acts is 1 in the intervention group and 3 in the control group. .

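### With about 23 participants per arm and over-dispersed counts, the robust-variance Wald test for efficacy does not hold its stated 0.05 level

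*Protocol*

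**What the plan says.** Protocol section 7.3 sets the size: "Each arm will have a total of approximately 23 participants". Its power simulation draws counts from a negative binomial distribution with variance phi times the mean, for phi = 1, 2 and 5, and labels the last two mild and severe over-dispersion.

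Section 7.6.2 plans a Poisson GEE for the count endpoints. On the variance: "A robust variance estimator will be used to correct for correlation among the longitudinal measures at baseline and post-intervention follow-up visits". On the test: "A Wald test will be used to test whether the intervention has significant effect on reducing sexual risk behaviors compared to the control arm", followed by "It will be a two-sided test at a significance level of 0.05". On the model: "If over-dispersion exists, quasi-Poisson or negative binomial model will be used". No criterion for over-dispersion is given, and no rule for choosing between the two alternatives.

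For sparse data the section adds that "the negative binomial assumption might not hold and a non-parametric approach will be considered". In that case counts would be grouped into two or three categories and compared by Fisher exact test at each visit. No small-sample correction, t reference or permutation test is named for the GEE comparison.

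**The concern.** A robust (sandwich) variance is justified when there are many independent units. Here there are 46, and repeated visits do not add to that number. With skewed counts a few heavy reporters largely determine the variance estimate, which is then too small on average and very variable. Comparing the Wald statistic with a normal cutoff then rejects too often.

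The protocol recognizes the small sample elsewhere: sections 7.3 and 7.6.1.1 choose exact binomial intervals for that reason. The between-arm efficacy model gets no such treatment.

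At stake is how a significant result, or a confidence interval, would be read. Section 2.3 justifies randomization partly by the effect size it will give for a possible larger study. Standard errors that are too small would make that estimate look more precise than it is.

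**Working it through.** **Inputs.** n = 23 per arm, 1:1; negative binomial counts with mean mu and variance phi × mu; phi = 1, 2, 5; one observation per person in the power calculation (all section 7.3). Two-sided 0.05 (section 7.6.2). Baseline plus eight follow-up assessments (section 2.3). The null means of 0.5 to 3 are assumed; Table 6 uses arm means from 0.5 to 3.5.

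**Statistic.** For an arm-only log-link model with complete data and independence working correlation, the estimate is log(m1/m2), where m1 and m2 are the arm means. The robust variance is

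SE² = Σ(y1i − m1)²/(n·m1)² + Σ(y2i − m2)²/(n·m2)²,

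and the test rejects if |log(m1/m2)|/SE exceeds 1.96. For pooled visits, y is the participant's mean over visits.

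**Step 1: the protocol's own power figure.** Section 7.3 states that "a sample size of 23 in each group would yield 92 percent (62 percent) power to detect the mean difference of 2" at phi = 2 (5), "if the mean of sex acts is 1 in the intervention group and 3 in the control group". In 10,000 simulated trials the robust Wald test gives 92.9% (63.5%) and a quasi-Poisson Wald test gives 92.7% (61.6%). Both are within 2 points of the stated figures. No single variant matches every over-dispersed cell of Table 6; the robust Wald test is 2–4 points high in about half of them.

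**Step 2: rejection under the null, uncorrected robust Wald, nominal 5%, means 1 to 3.** These runs used 20,000 single-visit trials and 40,000 longitudinal trials, the latter with a shared gamma frailty.

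| Comparison | phi = 1 | phi = 2 | phi = 5 |
|---|---|---|---|
| Single visit | 5.7–6.1% | 6.6–7.2% | 7.4–10.3% |
| Mean of 8 visits | 6.0–6.4% | 6.5–7.3% | 7.5–10.2% |
| Arm-by-period contrast | not run | 6.5–6.9% | 7.6–10.1% |

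At mean 0.5 and phi = 5 the rates are 11.4% (single visit) and 14.5% (pooled). A repeat single-visit run gave 6.5–7.2% at phi = 2, 7.4–10.0% at phi = 5, and 11.2% at mean 0.5. Averaging over visits does not remove the excess. By duality, a nominal 95% interval covers a true ratio of 1 in 92.8–93.4% of single-visit trials at phi = 2 (100 − 7.2 to 100 − 6.6). At phi = 5 it does so in 89.7–92.6% (100 − 10.3 to 100 − 7.4).

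**Step 3: is the model switch a cause?** If the robust variance is kept, the three models give the same estimate and standard error in this comparison, so the switch changes nothing. If model-based variances are used after an over-dispersion test, the negative binomial Wald test rejects 6.2–7.9% and quasi-Poisson with its own variance 5.3–5.8%. Taking any significant result of the three gives 7.1–10.7%.

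**Step 4: remedies.** Bias-corrected robust variances (Kauermann-Carroll, Mancl-DeRouen) with a t reference on 2 × 23 − 2 = 44 degrees of freedom give 4.7–5.8% at phi = 2 but still 5.7–8.8% at phi = 5. A permutation test of the same Wald statistic (4,000 trials, 999 permutations) gives 4.7–5.1% at both; a repeat run gave 4.2–4.7%.

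Power for 3 versus 1 at a single visit, on the same data:

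| Test | phi = 2 | phi = 5 |
|---|---|---|
| Uncorrected Wald | 92.7% | 64.5% |
| Permutation | 90.5% | 56.1% |

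The repeat run at phi = 5 gave about 63% and 54%.

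**The case against.** - **The protocol does not say uncorrected.** This stands as a limit. The reading rests on silence, and a statistical analysis plan that is not at hand could add a correction. But the protocol does fix a robust variance, a Wald test and a level, and these together do not deliver that level. The customary correction would not fully repair it under severe over-dispersion either.
- **The largest excesses occur where the protocol offers an exact method.** At phi = 5, r = mu/4 and P(0) = 0.2^(mu/4), so 82% of counts are zero at mean 0.5 and 67% at mean 1. The Fisher fallback covers that region, and this limits the consequence. It is only to be considered, though. It works visit by visit on grouped counts and gives no rate ratio, so it does not repair the Wald test.
- **The mild case is weak.** A small run with a full GEE fit at mean 2, phi = 2 gave 5.0%. With 400 trials its standard error is √(0.05 × 0.95/400) = 1.1 points, so it cannot exclude 6–7%. The larger runs show a modest but consistent excess.
- **The comparison is secondary and expressly unpowered.** This is correct, and it caps the importance of the point.

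A reader might also infer that the open choice of count model is what breaks the level. Step 3 does not support this: the switch has no effect while the robust variance is kept, and one of its branches, quasi-Poisson with its own variance, nearly holds 0.05. The switch matters only if model-based variances are used or the most favorable result is picked.

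**Conclusion.** The point holds for the robust-variance Wald test taken as written. Its real two-sided level is about 6.5–7% at phi = 2 and about 7.5–10% at phi = 5 for means 1 to 3, and higher at lower means. Intervals are correspondingly too narrow. No bias in the effect estimate itself has been shown.

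The result assumes no dropout, no site adjustment, a frailty constant over visits, and no small-sample correction. Monte Carlo error is about 0.1–0.35 points on the level and 0.3–0.8 points on power.

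A reader might infer that the trial's main conclusions are at risk. They are not: feasibility is estimated as proportions from attendance records and acceptability is descriptive, so neither uses this test. The change is worth making because it is cheap and because the effect size may inform a later trial.

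**What to change.** In section 7.6.2, or in the statistical analysis plan if it governs:

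- Keep the log-link GEE estimate of the rate ratio.
- Take the p-value from re-randomizing arm labels within site, since section 7.4 stratifies the randomization by site. State in advance how a relabelled arm with no acts is handled, because the log ratio is then undefined.
- Obtain the interval by inverting that test. For a ratio of counts this needs an assumed constant multiplicative effect and is approximate. The alternative is a bias-corrected robust standard error with a t reference, with a statement that it still under-covers somewhat under severe over-dispersion.
- Name one variance approach in advance in place of the open over-dispersion switch, and keep the negative binomial fit as a sensitivity analysis.

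The cost is a short program, wider intervals and lower nominal power. For 3 versus 1 at a single visit, power is about 91% instead of 93% at phi = 2, and about 54–56% instead of 63–65% at phi = 5. Part of that loss is simply the removal of the inflated level.
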